### Metformin (MET)

MET, an orally administered biguanide drug widely used to treat diabetes, has been shown to prevent diabetes in people with glucose intolerance, to reduce cardiac risk factors and prevent CVD in diabetics, and to improve clinical outcomes in patients with heart failure. Improved glycemic control in patients treated with metformin is associated with a decreased risk of diabetes related cardiovascular end points and all cause mortality when compared to conventional therapies that lower blood glucose to similar levels. Therefore, the cardioprotective effects of metformin cannot be attributed to its anti-hyperglycemic effects alone, but may be also related to the actions of metformin on lipid metabolism, vascular smooth muscle proliferation, cardiomyocyte calcium handling, endothelial function, hypercoagulation, and platelet reactivity. Such pleiotropic effects of metformin are largely mediated by the activation of AMPK, a protein that is normally activated in response to CR, which stimulates fatty acid oxidation, promotes glucose transport and glycolysis, inhibits neoglucogenesis and both triglycerides and protein synthesis.

Diabetes is associated with increased cancer incidence. However, several observational studies (mainly retrospective cohort studies) showed that diabetic patients treated with metformin have a significantly lower risk of developing cancer (all sites combined) than those untreated or treated with other drugs. MET may reduce cancer risk through two main mechanisms:

1st) reducing insulin resistance and therefore insulin, testosterone and IGF-I concentration in blood, and

2nd) activating AMPK, thus mimicking the effect of CR. AMPK activation results in downregulation of mTORC1 and IGF1/Akt pathways, and in p53-mediated cell cycle arrest. MET also inhibits IRS-1, thus preventing the feed-back activation of Akt that may follow mTOR inhibition.

In a phase-2 randomized study we recently showed that 1500 mg/day of metformin for 5 months significantly decreases body weight (-2.8 kg,  $P < 0.01$ ), and blood levels of glucose and insulin, improving insulin sensitivity (HOMA-IR index -0.23,  $P = 0.02$ ), while 1000 mg/day elicit only minor effects. In this study MET1500mg also reduced the plasma concentration of testosterone (-0.07 ng/mL,  $P < 0.01$ ), and increased SHBG (+10.6 nmol/L,  $P < 0.01$ ), which in older women are associated with insulin resistance, metabolic syndrome, CVD and breast cancer. Estradiol also decreased significantly in women who lost weight.

MET is a very safe drug used since 50 years to treat diabetes and more recently to prevent diabetes in people with glucose intolerance. As phenformin, a drug acting through the same mechanism, caused several cases of lactic acidosis, the issue was raised that also MET might cause such a serious side effect. As stated in a recent Cochrane systematic review, however, "There is no evidence from prospective comparative trials or from observational cohort studies that metformin is associated with an increased risk of lactic acidosis, or with increased levels of lactate" (Cochrane Database Syst Rev. 2006 Jan 25;(1):CD002967). Nevertheless we will carefully exclude from the study any person with chronic hypoxemic conditions that may be associated with lactic acidosis, such as cardiovascular, renal, hepatic and pulmonary disease, or under treatment with drugs that might interfere with MET clearance (see operative protocol). A physician will be available 24h/24 to answer questions on the phone if the participants do not feel well for whatever reason.

### **Molecular pathways that mediate the preventive effects of CR and of MET**

Specific DNA methylations and histone modifications, usually associated with pro-inflammatory micro-environment have been implicated in several ArCD (cancer, CVD, obesity, COPD). Global hypomethylation and site-specific hypermethylation are common features of human tumours and have been detected also in atherosclerotic lesions. Diet can profoundly alter epigenetic patterns, but the causal link between diet and epigenetics in the development of human disease is still poorly understood. A challenging research field is developing to determine which adverse epigenomic marks are reversible by specific drugs, nutrients, or lifestyle changes. Besides CR, over 50 bioactive phytochemicals have been demonstrated to be active on DNA methyltransferase, or histone acetylase/deacetylase. Experimental studies on animals or cultured human cell lines support their role in the prevention of ArCD, but have often been conducted at concentrations far beyond those documented in humans. It is very difficult to predict from these results the effects of these substances on disease prevention in humans. There is increasing evidence, however, that continuous exposure at physiological concentrations can remodel the epigenome in a cumulative fashions. We will create a biorepository of blood samples, collected at two time points (before randomization, and after one year), to carry out mechanistic studies on the epigenetic changes induced by lifestyle modification and MET treatment. With independent financial support we intend to systematically explore the epigenetic changes induced by CR, MET and CR + MET. A financial request has been submitted to the Italian CARIPLO Foundation (see Funding ID).

### **Importance of the project**

Our important, innovative, and bold hypothesis is that we can prevent, or at least postpone, the occurrence of virtually all ArCD through a comprehensive change of several aspects of western lifestyle, supported by a chemopreventive agent that acts on the same genetic pathways affected by lifestyle factors, and that we will obtain a very high compliance. Our confidence derives from the metabolic success of previous dietary intervention studies on a few hundred subjects (the DIANA trials) and from the preliminary results of our ongoing DIANA-5 trial, in which we succeeded to recruit 2000 breast cancer survivors that have been randomized in a lifestyle intervention and a control group to study the effect of moderate CR and increased physical activity on the incidence of recurrences.

Changing so many aspects of lifestyle, and examining so many outcomes, we will not be able to understand what has caused what. This may be irrelevant from a pragmatic public health point of view, but is certainly relevant from an explicative point of view. Beside the basic "intention to treat" analysis of the trial, therefore, we will analyse the outcomes also as a function of compliance with the different lifestyle recommendations, and of their association with MET treatment. With repeated 24h food diaries, for instance, we will be able to disentangle the role of protein restriction from that of CR, and to explore the effect of specific foods. Results will not have the strength of a randomized design, but will help mechanistic interpretation. Continuing the observation beyond the presently planned 5 years we will also have the power to study several specific diseases.

b.

## **Methodology**

### **Main study hypothesis**

Our hypothesis is that a substantial fraction of ArCD incidence and mortality, of the order of 25-33%, could be prevented through a) a sustainable comprehensive change in lifestyle, including moderate calorie and protein restriction, Mediterranean/macrobiotic diet, and physical activity, and b) chemopreventive treatment with metformin, a drug whose mechanism include the activation of the same genetic pathways that are activated by CR and physical activity. An ancillary study will examine the epigenetic changes induced by the above treatments.

### **Study design**

Phase III randomized controlled trial on men and women with MetS to test the hypothesis that comprehensive life-style changes and/or metformin treatment prevent ArCD.

**Design:** 2x2 factorial: 2,000 volunteers will be randomized in four equal groups of 500 each, and allocated to the following treatments:

METFORMIN (1700MG/DAY) + ACTIVE LIFESTYLE INTERVENTION  
PLACEBO + ACTIVE LIFESTYLE INTERVENTION  
METFORMIN (1700 mg/day) alone  
PLACEBO alone

The metformin /placebo component of the study will be double blind.

**Main outcome:** Total incidence of ArCD, including cancer, coronary heart disease, stroke, diabetes. **Secondary outcomes:** changing prevalence of MS and its metabolic and anthropometric components, total mortality, total cancer incidence, incidence of diabetes, cardiovascular diseases, myocardial infarction, stroke. These outcomes have been selected as major objectives because they are fairly easily identifiable on clinical charts according to standardized criteria. Other MetS associated ArCD, however, will be registered in

the follow-up and may eventually contribute to the overall disease burden to be evaluated.

**Recruitment:** Potentially eligible persons will be recruited through cancer screening programmes, general practitioners, clinical units dealing with overweight and metabolic diseases, and the media. Interested persons will be invited to attend conferences in which we will illustrate in detail the study design and its implications. Paper tape measures will be available at the conference to help attendees to check their waist circumference, which is the basic eligibility criteria. Those above the threshold and without any obvious reasons not to be included, will be asked to sign the informed consent form, and will be given an appointment for the first clinic visit and blood sample donation.

**Inclusion criteria:**

Age 55-74, waist circumference equal or greater than 85 cm for women and 100 cm for men, plus at least two other factors among those defining the MetS

**Exclusion criteria:**

- Diagnosed diabetes (or baseline fasting glycemia above 7mmol/L at baseline examination)
- Cancer (except skin carcinoma) diagnosed in the last 5 years, or under treatment
- Excessive frailty: in absence of agreed-upon measurements parameters and cutoff points, we will exclude subjects under the lower 5th percentile of the muscular mass distribution estimated by impedance in previous studies
- Conditions that contraindicate the use of MET because might favour lactic acidosis
  - Renal, cardiac, hepatic, or respiratory insufficiency
  - Serum creatinine <124µmol/L, or proteinuria at baseline examination
  - Current treatment with K-sparing diuretics, or with proton pump inhibitors
  - Excessive alcohol consumption
- Distressing side effects of MET treatment. Nausea and diarrhoea typically occur in about one third of patients receiving MET for the first time at full dose. To avoid dropouts for gastrointestinal discomfort we will treat all volunteers with half the planned dose for one month in order to exclude intolerant subjects before randomization. Participants randomized in the intervention group will continue to take half a dose for one month and then shift to the full dose.

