### Follow-up

We will actively contact the participants for the whole duration of the study, and obtain copy of relevant clinical records. The availability of an efficient regional hospital discharge diagnosis information systems, and of an accessible national death index will make follow-up feasible and complete. The Lombardy region, moreover, is almost completely covered by a network of cancer registries, which will allow to retrieve pathology reports. We will retrieve records for all ArCD but we will first concentrate the analysis on cancer, coronary heart disease, stroke, and diabetes, for which we have already used the above follow-up procedures in several previous studies. For the registration of cancer cases we will follow the rules and definitions of the European Network of Cancer Registries (available at [www.iarc.fr](http://www.iarc.fr)). We will register cancer site, morphology, TNM stage, grade, and, for breast cancer hormonal receptor expression. For the definition of diabetes we will follow the criteria of the American Diabetes Association: a) Symptoms of diabetes plus casual plasma glucose concentration  $\geq 200$  mg/dl (11.1 mmol/l). Casual is defined as any time of day without regard to time since last meal. The classic symptoms of diabetes include polyuria, polydipsia, and unexplained weight loss, or b) FPG  $\geq 126$  mg/dl (7.0 mmol/l), or c) 2-h postload (75 g) glucose  $\geq 200$  mg/dl (11.1 mmol/l). d) In the absence of unequivocal hyperglycemia, these criteria should be confirmed by repeat testing on a different day.

Suspected deaths from Coronary Heart Disease (CHD) and Cerebrovascular Disease (CBVD) will be identified from mortality files when the codes ICD10 I20-I25, R96 and R98 (or E10-E14, I50, I70 in association with I20-I25), or, respectively, the codes I60-I69 (or codes E10-E14, I10-I15, I46, I49, and I70 in association with I60-I69), are reported as underlying cause of death. Fatal CHD and CBVD will be assigned only after verification against hospital discharge and clinical records.

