### Third meeting

**Final eligibility check on the basis of blood and urine examinations**

#### Further inclusion criteria:

- 1) fasting glycemia <126 mg/dl
- 2) serum creatinin <124 µmol/L
- 3) Proteinuria absent or traces (1+)
- 4) Presence of metabolic syndrome (waist circumference + two further traits)

**At this point eligible participants are invited to start taking metformin 425 mg day (half a pill) for 15 days and 850 mg/day (a single full pill) for the subsequent 15 days**

The meeting will include:

- clinical visit
- explanation on how to take the pills:
  - in the first 15 days the participant must take half a pill (425mg) of metformin per day, during a main meal (breakfast, lunch or dinner)
  - in the subsequent 15 days the participant must take a full pill (850mg) of metformin per day, during a main meal (breakfast, lunch or dinner)
- discussion of the possible side effects and invitation to contact the study physician, available 24h/24, in case of symptoms or questions
- if the participant miss taking one or more pills, he/she must not increase the dose in the following days, and must not throw away the unused pills, which must remain in the box and rendered to the study centre at the next meeting
- arrangement of the next meeting (after 30 days)
- each participant is given a leaflet with instructions

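### The serum creatinine exclusion has its sign reversed: the value that bars a volunteer in one list is required for entry in the other

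*Protocol*

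**What the plan says.** The protocol gives a creatinine value in two places.

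- **Methodology, Exclusion criteria.** Under the group headed "Conditions that contraindicate the use of MET because might favour lactic acidosis", one bullet reads "Serum creatinine <124µmol/L, or proteinuria at baseline examination". The bullet just above it excludes organ insufficiency, including renal.
- **Operative protocol, Third meeting, Further inclusion criteria.** Item 2 of the entry list reads "serum creatinin <124 µmol/L". The meeting is described as "Final eligibility check on the basis of blood and urine examinations", and the run-in drug follows directly: "At this point eligible participants are invited to start taking metformin 425 mg day (half a pill) for 15 days".

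Four other places bear on kidney function without giving a creatinine value:

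- the neighbouring organ-insufficiency bullet in the exclusion list;
- the metformin background, which says people with renal disease will be kept out;
- item 5 of the inclusion list at the First meeting, which rules out kidney insufficiency;
- the 9th meeting, where a new diagnosis of renal insufficiency is a reason to stop the drug.

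**The concern.** An exclusion rule and an entry rule for the same measurement should point in opposite directions. Here both carry the same sign at the same limit, so they cannot both be applied. Taken alone, the exclusion list would screen out the volunteers with lower creatinine and pass those with raised creatinine, under a heading meant to prevent lactic acidosis.

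What is at stake is a renal safety limit. All volunteers take metformin for one month before randomization, and two of the four groups of 500, so 1,000 of 2,000, are then assigned 1700 mg/day. A case report form or eligibility checklist built from the exclusion list would carry the reversed limit. The protocol also calls for eligibility checks at the 9th meeting and at the yearly meetings without restating the creatinine limit. Staff who need the number then have to go back to one of the two lists, and no rule in the protocol says which of them prevails.

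**Working it through.** No sample size, power or error-rate figure depends on this point. The check is to treat each rule as a set of permitted values and see whether the sets overlap. Let x be serum creatinine in µmol/L.

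**1. Creatinine as written**

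| Rule | Place | Values that pass |
|---|---|---|
| Exclude x < 124 | Methodology, Exclusion criteria | x ≥ 124 |
| Admit x < 124 | Operative protocol, Third meeting | x < 124 |
| Both together | | none |

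The intersection is empty. Read literally, nobody can enter the trial.

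**2. Which rule is reversed**

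The exclusion bullet sits in a group whose purpose is to keep out people for whom metformin is contraindicated, directly below a bullet excluding renal insufficiency. Keeping x ≥ 124 and rejecting x < 124 runs against that purpose. The four places that mention the kidney without a value all support the direction used at the Third meeting. They do not confirm the number 124; only the two lists state it.

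**3. A comparison inside the protocol**

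Fasting glycaemia is the other numeric laboratory limit that appears in both lists, so it shows how the pair is meant to work. Let g be fasting glucose.

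- The exclusion list bars "baseline fasting glycemia above 7mmol/L at baseline examination", so g ≤ 7 mmol/L passes.
- The Third meeting requires "fasting glycemia <126 mg/dl".
- The diabetes definition under Follow-up ties 126 to 7.0 mmol/L: the number 126 is followed by "mg/dl (7.0 mmol/l), or c) 2-h postload (75 g) glucose". So the entry rule is g < 7.0 mmol/L.
- Both together: g < 7.0 mmol/L. The lists agree everywhere except at exactly 7.0.

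Glycaemia changes direction between exclusion and entry, as it should. Creatinine does not. Of the two shared numeric limits, one has a non-empty joint range as written.

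**4. Creatinine after correction**

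| Rule | Values that pass |
|---|---|
| Exclude x ≥ 124 | x < 124 |
| Admit x < 124 | x < 124 |
| Both together | x < 124 |

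The two rules coincide at every value, and both shared limits then have a non-empty joint range. With > 124 in place of ≥ 124 they would still disagree at exactly 124 µmol/L.

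**The case against.** The contradiction itself is not in dispute. The case on the other side is about weight.

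- **The operational check is right.** The step-by-step screening in the Operative protocol carries the correct sign immediately before the first pill, and renal insufficiency is barred separately in both lists. This stands, and it is why the practical risk is low.
- **The harm route is hypothetical.** The protocol does not describe a form built from the exclusion list. A form with the reversed sign would reject everyone whom the Third meeting admits, so the mistake would probably surface quickly. This also stands as a limit on the likely harm. It does not make the text correct, and the later eligibility checks give no value of their own.
- **It could be a misread character.** The text was extracted by a program, and a few words elsewhere in the file are damaged. A misread sign cannot be excluded completely. But the bullet reads cleanly around the sign, and the opposite sign comes through properly in other places, such as the age strata for randomization and the waist limits at the First meeting. Nothing points to an artefact here.
- **The same bullet has another mismatch.** It excludes proteinuria without qualification, while the Third meeting accepts absent or trace (1+) proteinuria. That is true, but it is a separate point and does not affect the creatinine correction.

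**Conclusion.** The concern holds. The creatinine exclusion in the Methodology section is reversed, contradicts the entry rule at the Third meeting, and defeats the purpose stated above it. The size is one sign in one bullet, with one direct contradiction between the only two places that give a creatinine value. It is most likely a typographical slip.

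The correction should be made because this is a numeric renal safety limit in the formal eligibility criteria of a drug trial. The chance of a participant being harmed is low for the reasons already given, and no statistical quantity changes. The conclusion rests on two assumptions: that the extracted sign is the one printed in the protocol, and that 124 µmol/L is the intended limit, as both lists state.

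**What to change.** In the Methodology exclusion criteria, change the creatinine bullet so that it excludes serum creatinine ≥124 µmol/L. Leave the entry rule at the Third meeting as it is. Use ≥ rather than >, so that a value of exactly 124 is treated the same way in both lists.

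The cost is one character in one bullet. No other criterion, no procedure and no calculation in the protocol has to change. Any eligibility form already drawn up should be checked against the Third meeting list.

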#### Inclusion criteria:

1. waist circumference > 85 cm for women and >100 cm for men
2. age between 55 and 74
3. no diagnosis of cancer in the last 5 years (except skin carcinomas)
4. no diabetes (IDDM and NIDDM),
5. no kidney insufficiency
6. no acute or chronic hepatitis
7. no diagnosis of coronary heart disease, myocardial infarction, stroke, hearth failure
8. no neurodegenerative disease
9. not under treatment with the following drugs:
  - Cimetidine, Ranitidine
  - Sulfamethoxazole + Trimetoprim (Bactrim, Chemitrim, Eusaprim)
  - Nifedipine (Adalat, Nifedidor, Nifasal, Nipin, Fenidina, Euxat, Coral, Citilat)
  - Furosemide (Lasix)
  - Diuretics with K retention: Amiloride (Moduretic), Triamterene, Spironolactone (Aldactone, Uractone, Spirolang)
10. availability to participate in the study for 5 years
11. for women aged 55-69, negative mammography in the last 12 months

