**9th meeting:**

**After 12 months of taking metformin or placebo at full dose, participants are invited for a new clinical visit, eligibility check, anthropometric measurements and blood and urine sample.**

In case of contra-indication to continue metformin treatment (e.g. for intervening diagnosis of renal insufficiency or major cardiovascular, metabolic or respiratory diseases) participants will be recommended to interrupt the drugs and to continue only the dietary intervention. The participant's general practitioner will be informed. If there are no contra-indications the participants will be given the pills for the next 12 months. At every meeting participants are invited to fill in a food frequency and physical activity questionnaire; this will allow the study dietician to reinforce lifestyle recommendations for those randomized in the active lifestyle intervention group. Participants randomized in the intervention group not showing significant improvements will be offered special teaching sessions.

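### The Methodology and the operative checklists state different safety exclusions, so a volunteer barred by the first can meet every listed check and take metformin in the run-in

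*Protocol*

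**What the plan says.** Eligibility is set out in three places in the Protocol.

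- **Background, Metformin (MET).** The protocol undertakes to keep out people with hypoxaemic conditions that may be associated with lactic acidosis. It names pulmonary disease among these, and adds people "or under treatment with drugs that might interfere with MET clearance (see operative protocol").
- **Methodology, Exclusion criteria.** Under conditions that contraindicate metformin because of lactic acidosis, it lists "Renal, cardiac, hepatic, or respiratory insufficiency", "Current treatment with K-sparing diuretics, or with proton pump inhibitors" and "Excessive alcohol consumption", together with creatinine and proteinuria criteria. A separate frailty bullet excludes people in the lowest 5% of the "muscular mass distribution estimated by impedance in previous studies".
- **Operative protocol.** The first meeting has eleven inclusion items. Item 9 requires that the volunteer is "not under treatment with the following drugs" and then lists "Cimetidine, Ranitidine", sulfamethoxazole with trimethoprim, nifedipine, furosemide and the potassium-retaining diuretics. The third meeting is the final eligibility check and adds four items: fasting glycaemia, creatinine, proteinuria and presence of metabolic syndrome. The fourth meeting checks residual pills, side effects and willingness to continue.

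Volunteers who pass the third meeting are invited to start metformin at 425 mg/day for 15 days, then 850 mg/day for 15 days. Randomisation follows the fourth meeting.

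**The concern.** The operative checklist is what staff apply to each volunteer, and the Background section names it as the place where interfering drugs are handled. It is not the list that the Methodology gives. Some conditions that the Methodology treats as metformin contraindications have no line in any operative check, and most of the drugs that the operative list bars are not in the Methodology.

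The first thing at stake is safety. The run-in gives active drug to everyone who passes the third meeting, including those later randomised to placebo, so a gap in the checklist exposes people before any allocation. The second is consistency. Two members of staff working from different sections could decide differently about the same volunteer, so the eligible population is not uniquely defined.

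**Working it through.** No figure in the plan depends on this point, so the check is an item-by-item comparison.

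| Item | Methodology, Exclusion criteria | First meeting (11 items) | Third meeting (4 items) | Fourth meeting |
|---|---|---|---|---|
| Respiratory insufficiency | barred (lactic acidosis) | absent | absent | absent |
| Excessive alcohol | barred (lactic acidosis) | absent | absent | absent |
| Proton pump inhibitors | barred (lactic acidosis) | absent | absent | absent |
| Low muscle mass | barred (frailty) | absent | absent | absent |
| Potassium-sparing diuretics | barred (lactic acidosis) | barred | – | – |
| Cimetidine | not named | barred | – | – |
| Ranitidine | not named | barred | – | – |
| Sulfamethoxazole + trimethoprim | not named | barred | – | – |
| Nifedipine | not named | barred | – | – |
| Furosemide | not named | barred | – | – |

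**Methodology items with no operative check:** 4. Three are lactic-acidosis items and one is a frailty item.

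**Operative drugs not named in the Methodology:** 5, counting the combination product as one.

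**Drug classes in both lists:** 1, the potassium-sparing diuretics.

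Of the four organ insufficiencies in the Methodology, renal and cardiac have operative counterparts (kidney insufficiency, heart failure). Hepatic has a partial one (acute or chronic hepatitis). Respiratory has none.

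**Does any other text close the gap?**

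1. The Background cross-reference covers interfering drugs, so the five operative-only drugs can be reached from there. It does not help with pulmonary disease, because the operative protocol has no respiratory item. It does not help with proton pump inhibitors either, because the operative drug list omits them.
2. Baseline requirements include a questionnaire on medical history and risk factors and an impedance measurement. Clinical visits take place at the second and third meetings. These could supply the information, but no operative step applies a respiratory, alcohol, proton pump inhibitor or muscle-mass criterion to it. The third-meeting check is described as resting on blood and urine results.
3. The Randomization section speaks of an eligible participant without saying which list decides that. A check at that point would also come after the 30 days (15 + 15) of run-in metformin.

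**Result.** A volunteer with, for example, respiratory insufficiency who otherwise qualifies meets all eleven first-meeting items and all four third-meeting items, and is invited to start metformin, although the Methodology excludes that person.

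**The case against.** The strongest reply is that the two lists are cumulative: the Methodology sets the exclusions, and the operative protocol is a practical screen added to them. The first meeting only registers potentially eligible people, the third adds further criteria, and physicians see the volunteers and their histories. On that reading the five operative-only drugs cause little trouble, since the cross-reference brings them in.

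This has force and narrows the point. It weakens any claim that every listed difference produces opposite decisions. It does not remove the other gap: if the Methodology exclusions also bind, the forms meant to enforce them lack four of the items. Having the information available is not the same as having a criterion that someone must apply.

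A reader might go further in three ways that the documents do not support.

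- **The 12-month visit.** It may be tempting to read the ninth-meeting text as showing that conditions present at entry emerge later as stopped treatment. That text concerns an "intervening diagnosis of renal insufficiency or major cardiovascular, metabolic or respiratory diseases", that is, disease arising after entry. It does not name alcohol, proton pump inhibitors or muscle mass.
- **Loss of power.** One might infer that wrongly admitted participants stop treatment and dilute the metformin comparison. The documents give neither the prevalence of these conditions nor a rate of stopping because of them, so any power figure would rest on unanchored assumptions.
- **Muscle mass as a drug-safety item.** The Methodology lists it as frailty, apart from the metformin contraindications. It is an eligibility difference only.

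**Conclusion.** The point stands as an internal contradiction in the stated eligibility rules. Three lactic-acidosis exclusions and one frailty exclusion in the Methodology have no operative check. Five drugs barred operatively are not named in the Methodology. The Background undertaking on pulmonary disease has no operative criterion. The missing checks remain whether the lists are read as alternatives or as cumulative; only the weight of the five-drug difference depends on that choice.

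Its importance rests on screening before active drug is given and on consistent eligibility decisions. No number of affected volunteers, effect on power or consequence for later treatment stopping is claimed. The comparison assumes that the operative items as printed are the criteria staff apply. Site forms that are not shown could carry more lines, but the protocol does not say so.

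**What to change.** Reconcile the Background section on metformin, the Methodology exclusion criteria and the first- and third-meeting criteria of the Operative protocol into one eligibility list. The responsible clinicians should decide, item by item, which conditions and drugs belong on it; this review takes no position on that. Have the other sections refer to that list rather than restate it, and print the identical list on the first- and third-meeting eligibility forms, so that every item is checked before run-in metformin is dispensed.

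The change concerns entry only. Whether any item should also govern continuation at the ninth and later meetings is a separate clinical decision and is not proposed here.

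The cost is one protocol clarification and one updated form, with possibly a slightly different screening yield. Sample size and analysis do not change.
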